#### Current Treatment for Aromatase Inhibitor-Induced Joint Pain

Non-steroidal anti-inflammatory drugs (NSAIDs), the most common medications used to treat pain associated with arthritis, may lead to serious renal and gastrointestinal toxicity, particularly in older adults. (76, 77) Selective cyclooxygenase-2 (COX-2) inhibitors, such as rofecoxib and celecoxib, are effective analgesics with fewer gastrointestinal side effects but have recently been shown to elevate the risk of cardiovascular events. (78) Non-toxic treatments that effectively relieve AI-induced musculoskeletal pain are needed. Ongoing studies are evaluating the potential benefits of physical activity, vitamin D, glucosamine/chondroitin and omega-3 fatty acids for treating this toxicity.

Since research in this area is limited, a small pilot study evaluating the use of acupuncture to relieve symptoms of AI-associated arthralgias was initially conducted. In this study of 21 women treated with a 6-week course of total body and auricular acupuncture, improvements were reported in pain severity, pain-related functional outcomes, and physical well-being, and no significant adverse events were reported. (79) This study was limited due to its small sample size and lack of an adequate control group. Investigators then went on to conduct a randomized, blinded, sham-controlled study in 38 breast cancer patients with AI-associated arthralgias. (80) True acupuncture for 6 weeks was associated with about a 50% decrease in mean BPI-SF scores compared to sham acupuncture with superficial needling at non-acupuncture points. Similar findings were seen for the WOMAC and M-SACRAH scores. Results found that acupuncture is an effective and well-tolerated strategy for managing this common treatment-related side effect.

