- \_\_\_\_\_ 5.5 Patients must have completed the **S1200** Brief Pain Inventory-Short Form (BPI-SF) (Form #40963) within 14 days prior to registration. Patients must have a worst pain score of at least 5 on the Brief Pain Inventory (item #2) that has started or increased since starting AI therapy.
- \_\_\_\_\_ 5.6 Patients must have a Zubrod performance status of 0 to 1 (see Section 10.3).
- \_\_\_\_\_ 5.7 Patients must not have had prior acupuncture treatment within the past 12 months or for AI-induced joint symptoms at any time.
- \_\_\_\_\_ 5.8 Patients must not have a severe bleeding disorder.

**SWOG Patient No.** \_\_\_\_\_

**Patient's Initials (L, F, M)** \_\_\_\_\_

- \_\_\_\_\_ 5.9 Patients must not have concurrent medical/arthritis disease that could confound or interfere with evaluation of pain or efficacy including: inflammatory arthritis (e.g., rheumatoid arthritis, systemic lupus, spondyloarthropathy, psoriatic arthritis, polymyalgia rheumatica), gout, episodes of acute monoarticular arthritis clinically consistent with pseudogout, Paget's disease affecting the study joint (knees/hands), a history of septic arthritis or avascular necrosis or intra-articular fracture of the study joint, Wilson's disease, hemochromatosis, alkaptonuria, or primary osteochondromatosis.
  
- \_\_\_\_\_ 5.10 Patients must not have a history of bone fracture or surgery of the afflicted knees and/or hands within 6 months prior to registration.
  
- \_\_\_\_\_ 5.11 Patients must not have a history of illness that, in the opinion of the investigator, might confound the results of the study or pose additional risk to the patient.
  
- \_\_\_\_\_ 5.12 Patients must not be on narcotics within 14 days of registration.
  
- \_\_\_\_\_ 5.13 Patients must not have received oral corticosteroids, intramuscular corticosteroids, or intra-articular steroids within 28 days prior to registration.
  
- \_\_\_\_\_ 5.14 Patients must not have received topical analgesics (e.g., capsaicin preparations) or any other analgesics (e.g., opiates, tramadol, with the exception of NSAIDs and acetaminophen) within 14 days prior to registration.
  
- \_\_\_\_\_ 5.15 Patients must not have received or implemented any other medical therapy, alternative therapy or physical therapy for the treatment of joint pain/stiffness within 28 days prior to registration. Therapeutic massage is allowed.
  

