#### 7.6 Acupuncture Treatment

##### a. Acupuncture Schedule

Patients will be randomized (2:1:1) to true acupuncture vs. sham acupuncture vs. waitlist control. Patients will be blinded to true acupuncture vs. sham acupuncture. Patients will not be blinded to the waitlist control. The study intervention is to begin within 5 working days of registration.

- True acupuncture administered twice weekly for 6 weeks followed by weekly treatments for 6 weeks (12-18 sessions total over 12 weeks).
- Sham acupuncture administered twice weekly for 6 weeks followed by weekly treatments for 6 weeks (12-18 sessions total over 12 weeks).
- Duration of intervention – Study intervention will be continued for 12 weeks unless unacceptable toxicity occurs, the subject has concurrent illness that necessitates withdrawal or subject decides to withdraw from participation for any reason. If the subject’s medical condition is influenced by the knowledge of which study intervention she was assigned, there will be unblinding upon the Investigator’s request.

- A licensed Study Acupuncturist(s) designated at each site will administer the true and sham acupuncture treatments.
- After the 24-week visit, all patients will receive a voucher for 10 free true acupuncture sessions administered by the Study Acupuncturist(s) and to be used at the patient's convenience and documented in the web-based calendar.

During the first 6 weeks of acupuncture, the twice weekly acupuncture sessions should be at least 24 hours apart and if a session is missed, it may be made up the following week for up to 3 sessions per week. The schedule will be flexible to allow for 8-12 sessions during the first 6 weeks, which may be more reflective of what may happen in the "real world" setting. During the second 6 weeks of weekly maintenance acupuncture, there will be no make-up of missed sessions, so patients may have only 1 session per week during the second 6 weeks of the study intervention (Week 7 to 12). Breaks of up to 30 consecutive days are allowed.

b. Documentation of Acupuncture Visits

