7.8 Additional Instructions for Patient-Completed Questionnaires

If a patient goes off protocol intervention before the schedule for patient-completed questionnaires has been completed, please administer all patient-completed questionnaires at the scheduled assessment times, even if the patient has begun another treatment. The 6, 12, 24, and 52 week assessment times as well should be defined from registration.

The **S1200** Cover Sheet for Patient-Completed Questionnaires (Form #19445) is required with each set of patient-completed questionnaires indicating whether or not the assessment occurred, if assistance was required, and the location of the assessment. If one or all of the questionnaires were not administered, an overall reason must be indicated on the **S1200** Cover Sheet for Patient-Completed Questionnaires (Form #19445). Please see Section 15.2 for more detailed instructions for the questionnaires.

- 7.9 All reasons for study discontinuation must be documented on the **S1200** Off Protocol Notice (Form #9707).
- 7.10 All patients will be followed for one year from registration. No further follow-up will be required once the patient completes the 52-week visit.

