For a 2-point difference and a 3.0 point SD at 6 weeks, with other parameters as specified above, 208 total eligible patients (104 true acupuncture, 52 sham acupuncture, and 52 waitlist control) would be required for 82% power for the two comparisons, based on two separate t-tests. [Note that in power calculations, the combination of the 5% non-adherence rate and the 10% contamination rate, stipulated above, reduces the nominal effect size of a 2 point difference to 1.7 points; while the 10% dropout rate inflates the estimated sample size by a factor of 1/0.9 or about 11%.] This approach allows two fully-powered independent comparisons between true acupuncture and the two alternatives. In addition, unlike an ANOVA approach, it does not assume equal variances across the three arms, which may be more appropriate in this setting given the inclusion of a waitlist control. Power will be higher with lower observed standard deviation.

A multiple linear regression analysis of the primary endpoint will include the baseline score as well as the pre-specified stratification factor. To allow for an ineligibility of 8% (based on a recent study, [S0715](#)), a total of 228 patients will be enrolled to achieve 208 eligible patients.

The potential for different dropout by arm, especially with respect to the waitlist control, will be mitigated by monthly conferences among study investigators to encourage proper assessment and submission of forms at every required timepoint for all patients. Dropout patterns will be monitored on an ongoing basis.

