#### Description of Waitlist Control

Patients randomized to the waitlist control group will undergo the scheduled evaluations at baseline, Week 2, Week 4, Week 6, Week 12, Week 24, and Week 52. Patients will be allowed to take acetaminophen and NSAIDs as needed for their joint symptoms, which will be documented as analgesic use at scheduled time points and captured on the **S1200** Supplemental Agents Reporting Form. They must agree not to join any other clinical trial for the treatment of AI-related arthralgias while participating in this study. After the 24-week visit, patients will receive a voucher for 10 free acupuncture sessions to be administered by the study acupuncturist(s) and used off-study at her convenience. Any additional acupuncture treatments received off-study will be recorded at 24 and 52 weeks. All of this information will be recorded on the **S1200** Assessment of Blinding and Additional Acupuncture Form (Form #20574).

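### Appendix 19.1 bars only waitlist women from joining another AI-arthralgia trial, which leaves an arm-dependent co-treatment rule in the open true-versus-waitlist comparison

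*Protocol*

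**What the plan says.** The bar appears once, in Appendix 19.1 under the description of the waitlist control: "They must agree not to join any other clinical trial for the treatment of AI-related arthralgias while participating in this study". The pronoun refers to the group that opens the paragraph: "Patients randomized to the waitlist control group will undergo the scheduled evaluations". The true and sham descriptions in the same appendix have no counterpart.

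The bar lasts as long as participation does. Section 7.10 sets that length for every arm: "All patients will be followed for one year from registration. No further follow-up will be required once the patient completes the 52-week visit". Section 7.8 tells sites to keep giving questionnaires to a woman who has left protocol intervention, "even if the patient has begun another treatment".

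Section 7.6a makes the waitlist comparison open: "Patients will not be blinded to the waitlist control". Section 11.1 makes true versus waitlist one of the two primary comparisons.

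The nearest rule for all arms is eligibility criterion 5.15, which excludes other therapy "for the treatment of joint pain/stiffness within 28 days prior to registration". It looks back from registration and says nothing about later trial entry.

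**The concern.** Section 7.1 gives the three arms the same visits, telephone contacts, questionnaires and functional tests. A bar on outside trial treatment written for one arm only departs from that. If women on true acupuncture may enter another trial and waitlist women may not, effective outside treatment could accumulate in one arm of an open comparison and be credited to acupuncture.

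Such trials existed. Section 2.0 says: "Ongoing studies are evaluating the potential benefits of physical activity, vitamin D, glucosamine/chondroitin and omega-3 fatty acids for treating this toxicity". Section 11.3 adds that the investigators had already recruited to other intervention studies for this complaint, supplements among them.

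At stake are mainly the assessments after the courses end. Section 1.2 uses Week 24 to judge how durable the response is once acupuncture stops, and outside treatment would blur that.

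**Working it through.** **1. Where a bar could sit.**

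| Place in the protocol | Bar on joining another trial? |
|---|---|
| Section 5, criteria 5.7 and 5.12 to 5.15 | No; they limit treatment before registration |
| Section 5, remaining criteria | No |
| Sections 7.1 to 7.10, including removal criteria in 7.7 | No, in any arm |
| Appendix 19.1, true acupuncture | No |
| Appendix 19.1, sham acupuncture | No |
| Appendix 19.1, waitlist control | Yes |
| Consent form | Not in the copy reviewed |

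True and sham are treated alike, so their comparison has no asymmetry. True and waitlist are not.

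**2. Number of women without the sentence.** Section 11.1 says "a total of 228 patients will be enrolled to achieve 208 eligible patients", and Section 6.0 gives 2:1:1 allocation.

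- Enrolled: 228 × 2/4 = 114 true, 228 × 1/4 = 57 sham, 57 waitlist. The bar covers 57/228 = 25%; the other 114 + 57 = 171 (75%) have no stated bar.
- Eligible: 104, 52 and 52, matching Section 11.1. The bar covers 52/208 = 25%; the other 156 (75%) have none.

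**3. The plan's power.** Inputs from Section 11.1: difference 1.7, SD 3.0, two-sided alpha 0.025, 10% dropout.

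- Evaluable women: 52 × 0.9 = 46.8 per control arm; 104 × 0.9 = 93.6 true.
- Standard error = 3.0 × √(1/46.8 + 1/93.6) = 0.537.
- 1.7/0.537 = 3.165; minus the critical value 2.241 = 0.924; power = Φ(0.924) = 82.2%.

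The noncentral t gives 81.5%. The stated 82% reproduces, and nothing in this point alters it.

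**4. When the asymmetry could matter.**

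- Weeks 0 to 6: true and sham women attend twice weekly. There is little time or reason to enter another trial before the primary endpoint.
- Weeks 6 to 12: weekly sessions continue.
- Weeks 12 to 24: 24 − 12 = 12 weeks with no study treatment in any arm and no vouchers yet. BPI-SF is taken at Weeks 16, 20 and 24.
- Weeks 24 to 52: all arms hold vouchers for true acupuncture, so Week 52 is already mixed.

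**5. Size.** If a share p of each arm enters another trial and the mean benefit there is b, the shift towards true acupuncture is b × (p_true − p_waitlist). The protocol gives neither p nor b. For scale only, assume b equals the 2 points that Section 10.1 calls clinically meaningful. Each percentage point of difference in uptake then moves the comparison by 2 × 0.01 = 0.02 points.

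**6. What the forms would show.** Form #9413 records pain medication, some other drugs, steroids, massage and dietary supplements in all arms. Form #20574 records acupuncture outside the study. A supplement trial would therefore leave a trace. No form asks about trial entry or exercise, so a physical-activity trial, one kind named in Section 2.0, would leave none.

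**The case against.** The best defence is that an undertaking by the patient belongs in the consent form, which every woman signs under criterion 5.19. If that form binds all arms, only a misplaced sentence remains. This stands as a limit on the finding, and the copy at hand cannot settle it.

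Next, silence is not permission. The sentence allowing acetaminophen and NSAIDs also sits only in the waitlist description, and nobody would infer that the other arms may not take them. A reader might conclude that the protocol deliberately lets true and sham women join other trials. The documents do not support that; a drafting slip is the likelier explanation. Even so, a site following the text would find the rule for one arm only.

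The direction is also uncertain. Waitlist women are barred from other trials but not from other treatment, and being untreated and unblinded they may have the strongest motive to seek it. Another trial may assign placebo or something ineffective. So the claim has to be that the asymmetry could favour true acupuncture, not that it would.

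Finally, Section 7.7 already continues assessments under intent-to-treat, and the forms capture many co-treatments. That reduces the consequence but does not make the rule equal across arms.

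**Conclusion.** The point holds as a cheap improvement. In the protocol text, the bar on joining another AI-arthralgia trial applies to waitlist women alone, so the stated rule differs by arm in the open true-versus-waitlist comparison and in no other comparison with true acupuncture. The secondary assessments at Weeks 16, 20 and 24 are the ones mainly exposed.

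Three stronger readings are not supported:

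- **That 171 of 228 women are exposed to outside trial treatment.** The figure counts women without the sentence. Nothing says how many would join.
- **That the primary result is biased.** At Week 6 any effect is probably negligible, given the short interval and the session schedule.
- **That 40 weeks (52 − 12) after the courses are at risk.** The vouchers mix the arms after Week 24, so the window that matters is 12 weeks.

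The conclusion assumes that the consent form does not already bar all arms, and that some outside trial treatment would help if taken. The as-randomised comparison remains usable.

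**What to change.** Move the sentence from Appendix 19.1 to Section 7.6 and reword it for everyone: women in all three arms agree not to enter another trial of treatment for AI joint symptoms while on study, that is, up to the Week 52 visit; any departure is recorded and the woman is analysed as randomised.

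Add one yes/no line to Form #9413 asking whether she has joined such a trial since the last assessment. That form is already completed at Weeks 16, 20 and 24, so no new contact is needed.

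The cost is one moved sentence, one form line and possibly matching consent wording. No sample-size or analysis change follows.

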## 19.2 Patient-Completed Questionnaires

Joint symptoms (Brief Pain Inventory-Short Form [BPI-SF], Western Ontario and McMaster Universities Osteoarthritis [WOMAC] index for the hips and knees, Modified-Score for the Assessment and Quantification of Chronic Rheumatoid Affections of the Hands [M-SACRAH], and PROMIS Pain Impact-Short Form [PROMIS PI-SF]) and quality of life (Functional Assessment of Cancer Therapy-Endocrine Subscale [FACT-ES]) will be collected from self-administered questionnaires given at baseline, 6 weeks, 12 weeks, 24 weeks, and 52 weeks. (137,139, 140,155)

The BPI-SF is a 14-item questionnaire which asks patients to rate pain over the prior week and the degree to which it interferes with activities on a 0 to 10 scale. (137) Severity is measured as average pain, pain right now, worst pain, and least pain. The BPI-SF responds to both behavioral and pharmacological pain interventions and has been well-validated. Note that we consider a reduction of two or more points on the BPI-SF worst pain item (#2) to correspond to a clinically meaningful decrease in pain.

The WOMAC index Version 3.1 is a validated questionnaire for assessing osteoarthritis of the knees or hips and consists of 24 questions related to three subscales: pain (0-50), stiffness (0-20), and physical function (0-170). (139) Each question is answered by the patients along a standardized 10-point scale with terminal descriptors. The WOMAC (V3.1) osteoarthritis index has been tested extensively for validity, reliability, and responsiveness for measuring changes in symptoms after different interventions. Although originally developed as a standardized assessment to evaluate osteoarthritis, the WOMAC has been used as a generalized symptom scale to evaluate musculoskeletal pain from conditions such as rheumatoid arthritis, total knee replacements, femoral shaft fracture, and osteonecrosis of the femoral head. (155-159) The M-SACRAH consists of three domains assessing pain, stiffness, and functional status in patients suffering from hand osteoarthritis and rheumatoid arthritis, answered on 10-point scale. (140)

The Functional Assessment of Cancer Therapy-General (FACT-G) consists of four subscales including Physical, Social/Family, Emotional, and Functional Well-Being. We will focus on just Physical and Functional Well-Being for this trial. We will also use the Endocrine Subscale (ES) to monitor endocrine side effects caused by AIs, such as hot flashes and vaginal symptoms.(155) ACT scales have five response levels ("not at all" to "very much"), where higher scores reflect better well-being and fewer symptom problems.

### 19.3 Measurement of Blood and Urine Biomarkers

#### a. Blood Analyses

Patients will provide blood specimens at baseline, 6 weeks, 12 weeks, and 24 weeks for the measurement of serum hormone biomarkers (estradiol, FSH, LH) and inflammatory biomarkers (IL-6, IL-12, TNF $\alpha$ , CRP). Blood (~20 cc in two 10-ml red-top tubes) will be collected by standard venipuncture technique. Blood in the red top tubes is allowed to clot for 30 minutes to 1 hour (maximum) at room temperature, and centrifuged at 3,000 x g for 20 minutes immediately after clotting, or refrigerated or placed on ice for no more than 6 hours, and centrifuged at 3,000 x g for 20 minutes. Using a pipette, serum is then transferred to eight 1.8-ml Cryovials (1 ml each) and any extra serum should be aliquoted in a separate Cryovial.

Radioimmunoassays (RIAs) will be used to measure serum estradiol, FSH, and LH. Serum IL-6, IL-12, and TNF $\alpha$  will be determined by enzyme-linked immunosorbent assay (ELISA) using a commercially available kit (R&D Systems Inc., Minneapolis, MN). Serum hsCRP will be measured on the COBAS INTEGRA 400 plus system (Roche Diagnostic, Indianapolis, IN). All serum assays will be performed according to the manufacturer's instructions and conducted at the Irving Center for Clinical Research (ICCR) at CUMC by [name].

#### b. Urine Analysis

At baseline, 6 weeks, 12 weeks, 24 weeks, and 52 weeks, approximately 10 ml of urine will be collected. Using a pipette, urine is then transferred to five 1.8-ml Cryovials (1.5 ml each) and any extra urine should be aliquoted in a separate Cryovial. The urine specimens will be sent in bulk shipment at the end of study on dry ice to the Sports Medicine Research and Testing Laboratory in Salt Lake City. The urine assays will be performed using high performance liquid chromatography (HPLC) tandem mass spectrometry.

#### c. Genotyping Analysis

At baseline, patients will provide additional blood specimens for plasma/buffy coat to be used for genotyping analyses. Approximately 10 ml of blood will be drawn in a 10-ml EDTA purple-top tube (after the serum sample so that the plasma can be mixed without delay). Just prior to collection of the specimen, it is important to rotate the 10-ml purple-top tube to allow the EDTA solution to coat the inside of the tube. Following collection of the blood, the sample must be inverted gently 10-15 times to mix well.

Genomic DNA will be extracted from the buffy coat (gray layer of WBC) using standard RNase/proteinase K technique. All samples will be genotyped using the ABI PRISM 7900HT Sequence Detection System (Applied Biosystems, Foster City, CA) in a 96-well format. The fluorogenic 5' nuclease or TaqMan assay will be used to determine genotype in the *CYP19A1* aromatase gene. Genotyping will be done by laboratory personnel blinded to treatment assignment. All genotyping studies will be conducted in the laboratory of [name] (CUMC).

#### 19.4 Training of Study Acupuncturists to the Study Protocol

A web-based site initiation visit and formal training of the Study Acupuncturists and Clinical Research Associates (CRAs) administering the functional testing at each site will be performed at the time of study activation. At least two acupuncturists licensed with the appropriate certifications for the state at each site will be trained and certified annually in administering the protocol and will perform all treatments. Each site already has experience in conducting acupuncture clinical trials.

CUMC-supplied study materials, including single-use, sterile, and disposable acupuncture needles, acupuncture tables, a training manual and online training module of the point protocols for both the true and sham acupuncture interventions and a demonstration of the grip strength and 'Timed Get Up and Go' (TGUG) testing, will be provided to each participating site. In addition, sites will be supplied with standardized dynamometers for grip strength testing and stop watches for the 'Timed Get Up and Go' test.

The acupuncture training manual will consist of the following:

- Written point protocols and anatomic renderings of all true and sham acupuncture points
- Written description about basic clean needle technique and administration of true and sham acupuncture interventions
- Written explanation for filling out case report forms done by the Study Acupuncturist

The acupuncture online training module will consist of the following:

- Video recording of the true and sham acupuncture points on a human volunteer
- Video recording of true acupuncture needling intervention in 1-2 selected body points and the auricular points
- Video recording of the sham acupuncture needling intervention in 1-2 selected body points and auricular points (taping)

